### 2.1. Hypothesis

The study hypothesizes that hypertensive patients receiving the community pharmacy-based health intervention will achieve the following outcomes:Reduced systolic and/or diastolic BP;Improved treatment adherence and BP control to target levels;Reduced hospitalization and death due to cardiovascular events;Positive changes in lifestyle behaviors;Increased in HRQoL.

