### 2.2. Objectives

This study evaluates the effectiveness of community pharmacy-based interventions in controlling BP among hypertensive patients in Bangladesh and Pakistan. The study assesses both clinical outcomes and cost-effectiveness. The primary objective is to evaluate the impact of patient counseling and education by CPs on BP control and treatment adherence, followed by a cost-effectiveness analysis to demonstrate the value for money in public spending on hypertensive care. Specifically, the cost-effectiveness analysis will calculate the cost per unit (mmHg) of blood pressure reduction and the cost per HRQoL gained.

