## 3. Methods

### 3.1. Study Design and Settings

A two-arm parallel-group cluster-randomized controlled trial (cRCT) will be conducted among hypertensive patients in Bangladesh and Pakistan. In the first stage, two districts in Bangladesh were chosen randomly: Rangpur district and Chuadanga district. In the second stage, from each district, one subdistrict was selected randomly: Pirganj and Alamdanga. Finally, 20 pharmacies were chosen from each subdistrict to reach our target sample. The overall flow of the study is shown in Figure 1. Randomization clusters are community pharmacies. Each country will follow a two-arm cRCT design. According to a 4.65% BP reduction with a standard deviation of 49.78 [27], the estimated sample size for Bangladesh is around 3600 at 80% power and 5% significance. Approximately 10% of participants will be selected based on a Bangladesh sample from Pakistan (360 hypertensive patients from four pharmacies). The average number of hypertensive patients per pharmacy is 90. Due to financial limitations and logistical challenges, it is necessary to choose 10% of the participants from Pakistan. This decision was primarily influenced by the availability of resources and the specific focus of our research project. These limitations included budget constraints that impacted the scope of the study and logistical challenges related to the larger geographic and infrastructural differences between the two countries. Conducting a full-scale study in Pakistan similar to Bangladesh is not feasible with the available resources. However, by including participants from Pakistan, we aim to enhance the diversity within our study population, despite some similarities in sociodemographic profiles and health behaviors between the two countries.

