### 3.3. Randomization

Community pharmacies will then be randomized to one of two parallel groups (allocation ratio 1:1) using a computer-generated random number sequence. Participants and pharmacies will be assigned to intervention and control groups in a 1:1 ratio. To reach the target sample, every pharmacy needs to recruit 90 hypotensive patients. The randomization and study procedure are presented in Figure 1.

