### 3.8. Outcome Evaluation

The primary effectiveness of the outcome will be evaluated by changes in the SBP and DBP of the patients from baseline to final follow-up at 12 months post-intervention. The secondary outcome measures will include (1) BP controlled to target (SBP < 140 mmHg and DBP < 90 mmHg); (2) composite outcome of death (all-cause) or hospital admission due to CHD, heart failure, or stroke; (3) incremental cost per HRQoL gained from baseline to end of follow-up; (4) improvement in the knowledge of patients on healthy lifestyle; (5) change in dietary salt intake; (6) change in quality of life; (7) change in the prevalence of current smokers; and (8) the treatment adherence rate. Hypertensive patients with poor adherence to their treatment regimens experience uncontrolled blood pressure. Adherence to hypertension treatment is defined as following the treatment regimen agreed to with their physician. According to the previous literature [29,30,31], a reduction of 5 mmHg of SBP is considered clinically relevant as it has been found to be significantly associated with a risk reduction in CHD, stroke, and other serious cardiovascular events. Health service utilization parameters will include the number and reason for visits to physicians and hospital admission, and when further complicated, the death of the patient. The cost-effectiveness measures are incremental cost per mmHg BP reduction or cost per HRQoL gained from baseline to end of follow-up at 12 months. For determining dietary salt intake level, a 24 h urinary sodium measurement will be opted.

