### 3.10. Data Management

All data will be confidentially stored in computers and entered manually in spreadsheets. Findings will be available to authorized individuals for analysis and reporting purposes only. To ensure the privacy and accuracy of the study data, the datasheets will be in a password-protected server, and data entry will be reconfirmed and double-checked for any potential errors during input. The research data will be published in a manner that ensures participants’ anonymity. A unique identifier will be used to coordinate participants’ data across baseline and all follow-up stages. Patients will be coded as numbers, with the code key stored in a password-protected document, ensuring all safety precautions. The patients who will complete all the scheduled follow-ups will be included in the analysis of results. To avoid a withdrawal bias, a strict intention-to-treat technique will be considered in our analysis. Furthermore, the variable imputation method will be used to handle the missing data. After each intervention, an interim analysis will be performed by the main investigator.

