### 3.13. Statistical Analysis

All outcomes will be analyzed using the intention-to-treat principle. Descriptive statistics will be used to present baseline characteristics and outcome variables. Percentages and frequencies will be used for categorical variables, and means and standard deviations will be used for continuous variables. Baseline characteristics between the two arms will be compared with chi-square or Fisher’s exact test, as appropriate. A multilevel mixed model will be used to compare the differential changes in each outcome across the time points (T1, T3, and T5) to measure the primary and secondary outcomes. We will analyze group changes (with individual pharmacies treated as a random effect) using multivariable mixed linear and non-linear regression for normally and non-normally distributed data to account for the cluster randomization effects. Point estimates from cluster-adjusted models will be reported with 95% confidence intervals. Additionally, subgroup analysis will stratify data based on hypertension-related complications and the number of associated medications to estimate the effect of the interventions. For all two-tailed statistical tests, *p*-value < 0.05 will be considered statistically significant. We will perform all statistical analyses using R (version 4.1) and Stata software (version 17.0).

A cost-effectiveness analysis will be performed on the average total cost incurred in both arms, and incremental cost-effectiveness ratios expressed as incremental cost per (1) 1, 5, or 10 unit (mmHg) decrease in blood pressure; (2) one hospital admission reduced; (3) 1 day of hospital stay reduced over the previous 6 months among the survivors; and (4) HRQoL using data from EQ-5D-5L and mortality. We will calculate all cost data in US dollars, using the non-subsidized cost as of the study’s commencement.

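### Either SBP or DBP can meet the BP hypothesis, each tested at p<0.05 with no rule joining them, so the false-positive rate at 12 months is about 7% to 9.75%, not 5%

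*Protocol article*

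**What the plan says.** - Protocol article, section 2.1: the first hypothesised outcome is "Reduced systolic and/or diastolic BP". Either pressure is enough.
- Section 3.8: the primary outcome is "changes in the SBP and DBP of the patients from baseline to final follow-up at 12 months post-intervention". Both variables are named, and no rule says whether one or both must succeed.
- Section 3.13: "For all two-tailed statistical tests, *p*-value < 0.05 will be considered statistically significant".
- Section 3.1: "According to a 4.65% BP reduction with a standard deviation of 49.78", "the estimated sample size for Bangladesh is around 3600 at 80% power and 5% significance". This is one BP quantity, not split into SBP and DBP.
- Section 2.2: "The primary objective is to evaluate the impact of patient counseling and education by CPs on BP control and treatment adherence". Section 3.8 lists BP controlled to target and treatment adherence as secondary outcomes (1) and (8).
- Section 3.10: "After each intervention, an interim analysis will be performed by the main investigator". Section 3.6 places the two counselling sessions at baseline and month 6. Table 2 has BP measured in both arms at months 0, 6 and 12.
- Section 3.4: outcome evaluators are blinded. Pharmacists and research assistants are not, and the research assistants collect data from participants.

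**The concern.** A 5% significance level describes one test. Here two tests can each deliver the claim that BP was reduced, and each is allowed the whole 5%. If the intervention did nothing, the trial would have two chances of a significant result, and the overall chance would exceed the stated level. The primary objective blurs the claim further by naming endpoints that the outcome section ranks as secondary, so a reader of the final report could not tell from the protocol which result had to be positive.

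The interim sentence raises a different risk. BP will exist by arm at month 6, and the person named to analyse it is the main investigator. Nothing in the text separates that role from running the trial; section 3.2 has the principal investigator or a research assistant approach patients and seek consent. If by-arm results are known part-way, they can affect contact with patients, retention effort and the 12-month measurement, all partly in the hands of unblinded staff. Section 5 itself names high dropout as the main limitation, so uneven retention effort is a practical risk.

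**Working it through.** **1. Reproduce the plan's own figure.** Inputs from section 3.1: difference 4.65, SD 49.78, 80% power, 5% significance. Section 3.13 makes the tests two-sided, and section 3.3 gives 1:1 allocation.

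n per arm = 2 × (1.960 + 0.8416)² × 49.78² / 4.65² = 2 × 7.849 × 2478.05 / 21.6225 = 1799.04, rounded up to 1800. The total is 3600, with power 80.0%. A one-sided test would give 2836. The stated figure therefore rests on one two-sided test at the full 5%, with nothing set aside for a second endpoint.

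**2. Either-or success at 12 months.** Under no effect, let Z₁ and Z₂ be the SBP and DBP test statistics with correlation r. The error rate is P(|Z₁| > 1.96 or |Z₂| > 1.96). For r = 0 this is 1 − 0.95² = 9.75%. Other values come from the bivariate normal distribution. The document gives no SBP/DBP correlation, so r is an assumption shown over a range.

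| Assumed r | At least one significant, either direction | At least one significant in favour of the intervention |
|---|---|---|
| 0 | 9.75% | 4.9% |
| 0.3 | 9.5% | 4.8% |
| 0.5 | 9.1% | 4.5% |
| 0.6 | 8.8% | 4.4% |
| 0.7 | 8.3% | 4.2% |
| 0.9 | 7.0% | 3.5% |

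The reference values for a single test are 5% and 2.5%. Every row exceeds them, as it must for any r below 1. The calculation takes each test to hold its own 5% after adjustment for clustering.

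**3. What the interim look could add.** A look after the baseline session has no post-baseline BP, so there is one informative look, at month 6. Suppose, contrary to anything stated, that a significant month-6 result also counted as success at p<0.05. By simulation (1,000,000 draws), with assumed SBP/DBP correlations of 0.3 to 0.9 and assumed correlations between looks of 0.5 to 0.8, the error rate would be 10.8% to 16.9%. If month 6 cannot count as success and cannot stop the trial, the look adds nothing to the figures in step 2.

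**4. Ways to restore 5%, on the document's own inputs.**
- One primary BP variable, then the other in fixed order: 5% is held, and the calculated 3600 at 80% power stands.
- Bonferroni, 0.025 for each pressure: error at most 5% (4.3% at r = 0.7, 4.9% at r = 0). Power at 3600 falls to 71.3%. For 80% power, n per arm = 2 × (2.2414 + 0.8416)² × 2478.05 / 21.6225 = 2178.7, so 2179 per arm and 4358 in total.
- Both pressures must be significant: 5% is held, but joint power cannot be computed from the inputs given.

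**The case against.** The strongest objection concerns the interim analysis. A reader might infer that SBP or DBP, at month 6 or month 12, can each win at p<0.05, so that the trial's error rate is around 15%. Two places make this tempting: Table 2 ticks the primary outcome at both months, and section 3.13 compares changes across the three time points. Neither is a success rule. Section 3.8 fixes the primary evaluation at 12 months, section 3.10 mentions no efficacy test and no stopping, and section 3.13 does not refer to interim looks when it sets p<0.05. A descriptive look would leave the 12-month error rate untouched. This objection stands, and the larger figure should not be presented as a property of the plan.

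It is also fair to say that an article may leave interim purpose, boundaries and access to a fuller document, so their absence is not held against the plan. What the article does state is who performs the analysis and when. It does not say whether the comparison is by arm, so the risk to conduct is a possibility, not an established fault. Section 3.4 does promise blinded outcome evaluators, which reduces that risk. It does not remove it, because the staff who collect data are unblinded.

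On the endpoints, one could read section 3.8 as requiring both pressures to succeed, which would hold 5%. That reading contradicts the either-or wording of section 2.1. A separate analysis plan could add a correction, but only by departing from what this document fixes: an either-or hypothesis and p<0.05 throughout. BP control in section 2.2 may be loose wording for BP; adherence cannot be explained that way.

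**Conclusion.** The endpoint part holds as written. With either-or success at 12 months, the false-positive rate is about 7% to 9.75% against the stated 5%, for assumed SBP/DBP correlations from 0.9 down to 0. The exact value depends on a correlation that the document does not give; the direction does not. The mismatch between the primary objective and the secondary outcome list is a real inconsistency that does not enter this calculation. The interim sentence is a secondary matter of trial conduct. The range of 11% to 17% applies only under an efficacy rule at month 6 that the protocol does not contain. This is worth correcting before the 12-month data are analysed. The lack of any allowance for clustering in the 3600 is a separate question and plays no part here.

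**What to change.** 1. Name change in SBP from baseline to 12 months as the single primary endpoint. Section 3.8 already ties its 5 mmHg relevance criterion to SBP. Test DBP at 12 months next, at the same 5%, only if SBP is significant; otherwise report DBP descriptively. Align section 2.1 with this order.
2. Reword the primary objective in section 2.2 to name 12-month SBP, and leave BP control to target and adherence as secondary.
3. State in section 3.1 that the assumed difference and SD refer to SBP, if they do. The document does not say which pressure they describe, and the claim that 3600 still suits the single endpoint depends on it.
4. Replace the interim sentence in section 3.10 with wording such as: during follow-up only pooled data on recruitment, retention and data quality are reviewed, and no between-arm outcome comparison is made before the 12-month data lock.

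Cost: no extra patients on the document's own calculation, unlike an equal split of the 5%. DBP alone can no longer carry the primary claim, and the investigator gives up early by-arm results. Because the trial is registered, the change needs a dated protocol amendment and possibly a registry update, so it is more than an edit of wording.

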### 3.11. Adverse Event Reporting

We will consider that a participant may likely identify a medication-related issue during pharmacist counseling, either in the intervention or control group. However, given the nature of the study and the data collection procedure, the chance of this occurring is unlikely. If any concerns do arise, the patient’s doctor will be promptly notified.

### 3.12. Pilot Study

To test the feasibility and acceptability of the protocol, a pilot study will be conducted in two community pharmacies, involving five patients from Bangladesh and Pakistan. Three investigators will provide feedback on the process based on the pilot study findings and experiences. We will then confirm and review our logistics and make any necessary changes to the intervention process.

### 3.13. Statistical Analysis

All outcomes will be analyzed using the intention-to-treat principle. Descriptive statistics will be used to present baseline characteristics and outcome variables. Percentages and frequencies will be used for categorical variables, and means and standard deviations will be used for continuous variables. Baseline characteristics between the two arms will be compared with chi-square or Fisher’s exact test, as appropriate. A multilevel mixed model will be used to compare the differential changes in each outcome across the time points (T1, T3, and T5) to measure the primary and secondary outcomes. We will analyze group changes (with individual pharmacies treated as a random effect) using multivariable mixed linear and non-linear regression for normally and non-normally distributed data to account for the cluster randomization effects. Point estimates from cluster-adjusted models will be reported with 95% confidence intervals. Additionally, subgroup analysis will stratify data based on hypertension-related complications and the number of associated medications to estimate the effect of the interventions. For all two-tailed statistical tests, *p*-value < 0.05 will be considered statistically significant. We will perform all statistical analyses using R (version 4.1) and Stata software (version 17.0).

A cost-effectiveness analysis will be performed on the average total cost incurred in both arms, and incremental cost-effectiveness ratios expressed as incremental cost per (1) 1, 5, or 10 unit (mmHg) decrease in blood pressure; (2) one hospital admission reduced; (3) 1 day of hospital stay reduced over the previous 6 months among the survivors; and (4) HRQoL using data from EQ-5D-5L and mortality. We will calculate all cost data in US dollars, using the non-subsidized cost as of the study’s commencement.

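### Baseline patient characteristics are to be tested between arms with chi-square or Fisher tests that make no allowance for pharmacy clustering, so spurious significant differences are more likely than the nominal 5%

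*Protocol article*

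**What the plan says.** On the baseline comparison, section 3.13 (Statistical Analysis) states: "Baseline characteristics between the two arms will be compared with chi-square". The sentence goes on to offer Fisher's exact test as the alternative, whichever suits. That sentence does not mention clustering. The section also sets a two-sided 5% threshold for its tests, so the baseline p-values will be read as significant or not.

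On the design, section 3.1 states: "Randomization clusters are community pharmacies". It adds "The average number of hypertensive patients per pharmacy is 90" and, for Bangladesh, "Finally, 20 pharmacies were chosen from each subdistrict to reach our target sample". Two subdistricts were selected, which gives 40 pharmacies. Pakistan adds "360 hypertensive patients from four pharmacies". Section 3.3 allocates pharmacies 1:1.

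On clustering, section 3.13 puts a pharmacy random effect in the outcome models and reports cluster-adjusted estimates with confidence intervals. Neither an ICC nor a design effect appears anywhere in the article.

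**The concern.** A baseline test in a randomised trial asks whether the arms differ by more than the allocation alone would produce. Here the allocation acts on 40 pharmacies (44 with Pakistan), not on about 3600 patients. Ordinary chi-square and Fisher tests on patients build their null distribution as if each patient had been allocated independently. If patients of one pharmacy resemble each other in, say, education, occupation or religion, the difference between arms varies more than these tests assume. They then reject too often even when randomisation has worked.

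Section 3.13 treats the same feature of the design in two ways: it accounts for pharmacy when analysing outcomes but not when comparing baseline. At stake is a baseline table with p-values that are too small, which readers could take as evidence of failed randomisation.

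**Working it through.** **Inputs from the article.** Cluster size m = 90. Bangladesh has 2 × 20 = 40 pharmacies, 20 per arm at 1:1, and 40 × 90 = 3600 patients. Adding Pakistan gives 44 pharmacies and 3960 patients. The test is two-sided at 5%.

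**Input assumed.** The ICC of a baseline characteristic. The article gives none, so 0.001 to 0.10 is shown.

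**The plan's own figure.** Section 3.1 uses a difference of 4.65, an SD of 49.78, 80% power and 5% significance. The usual formula for two means, n per arm = 2 × (1.96 + 0.84)² × 49.78² / 4.65², with unrounded normal quantiles and rounding up, gives 1800 per arm and 3600 in total. The stated size is reproduced with a design effect of 1, so no ICC can be recovered from it.

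**Formula.** With equal clusters, the variance of the difference in proportions between arms is inflated by DE = 1 + (m − 1) × ICC = 1 + 89 × ICC. A test that ignores this has true size 2 × [1 − Φ(1.96 / √DE)].

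| Assumed ICC | DE | 1.96/√DE | True size of the nominal 5% test |
|---|---|---|---|
| 0 | 1.00 | 1.96 | 5.0% |
| 0.001 | 1.09 | 1.88 | 6.0% |
| 0.005 | 1.45 | 1.63 | 10.3% |
| 0.01 | 1.89 | 1.43 | 15.4% |
| 0.02 | 2.78 | 1.18 | 24.0% |
| 0.05 | 5.45 | 0.84 | 40.1% |
| 0.10 | 9.90 | 0.62 | 53.3% |

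**Check by simulation.** Beta-binomial data were generated with no true difference between arms: 20 or 22 pharmacies per arm, 90 patients each, prevalence 5%, 20% or 50%, and 20,000 runs per scenario. The ordinary chi-square test rejected in 4.9–5.2% of runs at ICC 0, 9.9–10.8% at 0.005, 15.1–15.4% at 0.01, 23.4–24.4% at 0.02 and 39.8–40.7% at 0.05. A t test on the pharmacy proportions, run on the same data, rejected in 4.6–5.3% throughout. Ignoring the clustering is therefore what inflates the rate. A smaller simulation at ICC 0.10 (20 pharmacies per arm, 4000 runs) gave about 54%. The 0.001 row rests on the formula alone.

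**The case against.** The strongest reply is that nothing of consequence depends on these tests. The effect estimates and their intervals come from models with a pharmacy random effect, and the baseline p-values do not enter them. This stands, and it limits the point to the baseline table.

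Several stronger readings are tempting, but the article does not support them.

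- *The tests reject true balance 15–40% of the time.* This is the result for ICCs of 0.01 to 0.05, not a known property of this trial. A weakly clustered characteristic gives 6–10%, a strongly clustered one over 50%.
- *The table will show several false differences.* What follows is a raised probability for each clustered characteristic. A count would also need the number of characteristics, their independence and an ICC for each, none of which is given.
- *Covariates will be chosen from these p-values.* Section 3.13 does not say so, and how covariates are fixed is commonly left to the analysis plan.
- *Chi-square will be applied to age, BP or BMI.* Section 3.13 summarises continuous variables by means and SDs, and its sentence on baseline tests ends with a qualifier that leaves room for other tests. In a condensed article, an unnamed test for continuous variables is missing detail and not an error.

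Two further replies hold in part. First, the article does not say that the tests are run on patients. That is still the natural reading, since most baseline items in section 3.7 are patient characteristics. The exceptions are pharmacist and pharmacy items: with one record per pharmacy, a Fisher test on these is not affected by patient clustering.

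Second, section 3.4 says that treated and control pharmacies will be drawn from clearly different locations. If location shapes allocation, some baseline differences could be systematic and not spurious. The rates above assume correct randomisation. The reply does not rescue the planned tests, because a test that ignores clustering cannot separate a systematic difference from ordinary variation between pharmacies.

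**Conclusion.** The point holds, and it is a limited one. As written, section 3.13 fixes baseline tests on patient characteristics that disregard the unit of randomisation, and their p-values are too small for any characteristic with a positive ICC. With 90 patients per pharmacy, the true size of the nominal 5% test runs from about 6% at ICC 0.001 to about 53% at ICC 0.10. These figures assume equal clusters of 90, correct 1:1 randomisation of pharmacies and the stated ICCs, which are assumptions and not figures from the article.

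A reader might infer that the primary analysis is compromised. It is not: the effect estimates come from cluster-adjusted models. What is affected is the reporting of the baseline table and the judgement of balance drawn from it.

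**What to change.** In section 3.13, replace the chi-square/Fisher comparison of patient characteristics with a descriptive baseline table by arm, for example with standardised differences. If p-values are wanted, take them from a comparison that accounts for pharmacy, either a model with a pharmacy random effect or a test on pharmacy-level summaries. Fisher tests on pharmacist or pharmacy characteristics with one record per pharmacy need no change.

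The cost is one reworded sentence. It needs no additional data and leaves the sample size and the outcome models as they are.

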### 3.7. Data Collection

Data will be collected primarily through a face-to-face interview with an open-ended structured questionnaire. The interview team will comprise graduates in social science, public health, demography, and statistics with extensive experience in survey techniques, along with two experienced supervisors who will oversee the survey. They will all undergo four days of mandatory training and two days of practical sessions focused on the questionnaire content, techniques to obtain more information from study subjects, and strategies for acquiring complete and valid data. An operational manual will be provided to both interviewers and supervisors to ensure clarity on the research purpose. The supervisor will be responsible for regularly monitoring the intervention process. The details about the data collection time point are mentioned in Table 2.

At baseline, after obtaining informed consent by the interviewer, data will be collected on the self-reported basic socioeconomic and demographic characteristics of the patients, such as age at the completion of the questionnaire, gender, highest level of education completed, occupation, religion, and marital status. Also, the basic characteristics of the CP (age, gender, and working experience in the community pharmacy in years) will be collected. Information on disease profiles will be obtained by face-to-face direct interview and used to inform the consultation at each stage. The following data will be requested from patients and CP at baseline and 12 months via questionnaire or pre-defined data collection form (as appropriate):Clinical factors of the patients [time since diagnosis of hypertension in years; types of concomitant antihypertensive medications; development of any hypertension-related complications such as coronary heart disease (CHD), and heart failure and stroke; in the previous six months: (i) occurrence of any adverse health condition related to hypertension requiring hospitalization; (ii) total number of days in hospital following admission; and (iii) total number of visits to doctors for hypertension and its related complication management;Organizational information of the community pharmacies (number of visits from hypertensive patients per month in last six months, number of hypertensive cases referred to hospital due to complications in last six months);Quality of life measure (EuroQol EQ-5D-5L) [28].

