** *Physical examination (Control and intervention group)* **												
Blood pressure measurement						x			x			x
BMI						x			x			x
Blood glucose measurement						x			x			x

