** *Outcome measurements (Control and intervention group)* **												
*Primary outcome*												
Change in SBP and DBP									x			x
*Secondary outcome*												
BP controlled to target									x			x
Composite outcome of death or hospital admission									x			x
Improvement in knowledge									x			x
Changes in lifestyle									x			x
Changes in drug adherence									x			x
HRQoL gained									x			x
Cost per unit of BP reduction									x			x
Cost per HRQoL gained									x			x

HRQoL, health-related quality of life; SBP, systolic blood pressure; DBP, diastolic blood pressure; BP, blood pressure.

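### The change-from-baseline rule in section 3.13 covers the death-or-admission composite, which has no true month-0 value and needs its own 12-month analysis

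*Protocol article*

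**What the plan says.** Section 3.13 prescribes: "A multilevel mixed model will be used to compare the differential changes in each outcome across the time points (T1, T3, and T5" and says this is done "to measure the primary and secondary outcomes". It makes no exception. It adds that group changes will be analysed, with pharmacy as a random effect, by "multivariable mixed linear and non-linear regression for normally and non-normally distributed data".

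Section 3.8 lists as secondary outcome (2) the "composite outcome of death (all-cause) or hospital admission due to CHD, heart failure, or stroke". No other between-arm effect analysis of it is named.

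In Table 2, T1 is month 0, T3 is month 6 and T5 is month 12. The row "Composite outcome of death or hospital admission" is marked at months 6 and 12 only. The row "Blood pressure measurement" is marked at months 0, 6 and 12. Section 3.6 numbers its sessions differently (T1 there is month 6), but the set T1, T3, T5 in section 3.13 matches only Table 2.

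Section 3.7 contains a six-month look-back item, "occurrence of any adverse health condition related to hypertension requiring hospitalization", under the lead-in "The following data will be requested from patients and CP at baseline and 12 months".

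On who is analysed, sections 3.10 and 3.13 both promise intention to treat, but section 3.10 also limits the analysis to patients who complete every scheduled follow-up, and plans imputation of missing data with no separate provision for deaths.

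**The concern.** A differential-change analysis needs the same variable before and after the intervention. Blood pressure, control to target and EQ-5D meet that condition. An incident event that includes death does not, because being alive at month 0 is a condition of enrolment. The rule as written nevertheless covers the composite, so an analysis plan that followed it would have to invent a T1 value.

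The composite is where the hypothesis of fewer hospitalisations and deaths (section 2.1) is tested, and the introduction names mortality and admissions, together with cost-effectiveness, as unexamined in these two countries. The risk is a secondary result with no valid confidence interval, or one measured against events that occurred before the trial, in place of the 12-month risk in each arm. The handling of deaths adds to this: read literally, the completer sentence removes every participant who died before the final visit from an outcome that counts death.

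**Working it through.** **Inputs.** From the document: about 3600 patients in Bangladesh, 1:1 allocation, two-sided 5%. The stated size reproduces: 2 × (1.960 + 0.842)² × (49.78/4.65)² ≈ 1,800 per arm, 3600 in total. That calculation is for blood pressure; the document gives no event rate, effect size or power for the composite. Assumed here: control risk p per six months, risk ratio 0.75, independence between patients and between periods, no clustering.

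**Does the composite have a T1 value?** The marks in Table 2 do not settle this, because change in SBP and DBP is also marked only at months 6 and 12. The difference is that blood pressure itself is measured at month 0, whereas the composite as defined in section 3.8 cannot be. Two ways of supplying a T1 value remain.

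**Reading (a): T1 = 0 for everyone.** A binomial logit model with arm, time and arm × time was fitted to cell counts with 1800 per arm, zero events at T1 and p = 2%, 5% or 10% at T3 and T5 (pharmacy effect left out).
- The T1 intercept does not converge: −9.6, −16.6 and −26.6 after 8, 15 and 25 iterations.
- The standard error of the arm × T5 term goes from about 2.4 to 80 to 11,871.
- The point value of that term stays at the follow-up log odds ratio: −0.293, −0.301 and −0.315.
- On the risk-difference scale the zeros cancel. The change contrast equals the follow-up difference: −0.5, −1.25 and −2.5 percentage points.

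**Reading (b): T1 = the pre-enrolment hospitalisation item.** This sets hypertension-related admissions before enrolment against death or cause-specific admission after it. For precision, use Var(log odds) = 1/[n p(1 − p)] with n = 1800, and assume the T1 risk equals p in both arms. Write V(p) for this variance.
- T5 minus T1: V(p) + V(0.75p) + 2V(p).
- T3 and T5 averaged, minus T1: ½[V(p) + V(0.75p)] + 2V(p).
- Cumulative 12-month comparison: V(2p) + V(1.5p).

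At p = 1%: V(0.01) = 0.0561, V(0.0075) = 0.0746, V(0.02) = 0.0283, V(0.015) = 0.0376. The three variances are 0.2430, 0.1776 and 0.0659.

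| Assumed p | SE, T5 − T1 | SE, mean(T3, T5) − T1 | SE, cumulative | Variance ratios to cumulative | Power, same order |
|---|---|---|---|---|---|
| 1% | 0.49 | 0.42 | 0.26 | 3.7 and 2.7 | 0.09, 0.11, 0.21 |
| 2% | 0.35 | 0.30 | 0.18 | 3.7 and 2.7 | 0.13, 0.16, 0.37 |
| 4% | 0.25 | 0.21 | 0.13 | 3.6 and 2.6 | 0.22, 0.29, 0.65 |

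The larger ratio has two parts. At 1%, subtracting T1 multiplies the variance of the T5 comparison by 1.86, and using only the T5 window in place of 12 months multiplies it by 1.98; 1.86 × 1.98 ≈ 3.7.

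**Deaths between T3 and T5.** Assume 5% control risk per period and 30% of first-period events fatal, so 1.5% have died by T3. The T5 proportion is then:
- 5.00% if the dead are dropped;
- 1.5% + 98.5% × 5% = 6.43% if they are carried as events;
- 98.5% × 5% = 4.93% if they count as non-events.

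The document does not say which applies.

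**The case against.** The strongest reply is that section 3.13 is a single condensed paragraph covering many outcomes. Its allowance for non-linear mixed regression with a pharmacy random effect already admits a mixed logistic model, and the coding of each binary outcome is commonly left to the full protocol or analysis plan. That excuses missing detail. It does not excuse a stated rule that expressly covers each outcome and cannot fit this one.

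Three stronger readings are tempting, and the documents do not support them.

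- A reader might infer that the effect is undefined however it is analysed. Section 3.13 names no link function. Under reading (a) only inference on the logit scale fails; on the risk-difference scale the contrast is the ordinary follow-up comparison.
- A reader might infer that the plan recounts deaths at T5, drops them from the denominator, or scores an early admission as improvement later. No text says any of these. What can be shown is that there is no carry-forward rule and that the completer sentence in section 3.10 conflicts with intention to treat.
- A reader might infer that the look-back item is the planned T1 value and that the trial loses 3.6 to 3.7 times its information. Section 3.7 collects the item as a clinical factor and nowhere makes it the baseline of the composite. The larger ratio also depends on ignoring T3, which the planned model includes, and on independence: if earlier admission predicts later admission, the variance of the change falls.

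The composite is also only one of eight secondary outcomes and was not powered, so the power figures contradict nothing in the document.

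**Conclusion.** The concern holds in a limited form. Section 3.13 applies a change-from-T1 analysis to a composite that has no true T1 value. The consequence depends on how the gap is filled: no usable logit-scale standard error if T1 is zero, or an effect measured against a different, admission-only variable if the look-back item is used. The mismatch follows from the definitions and needs no assumed rates.

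The precision cost under the second reading, a variance 2.6 to 3.7 times that of the cumulative comparison, is illustrative. It rests on assumed risks of 1% to 4% per six months, a risk ratio of 0.75, equal T1 risk in both arms, independence and no clustering. Clustering would lower all the power figures.

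The treatment of deaths is unresolved, and the completer restriction contradicts the intention-to-treat statements. The point should be corrected before analysis, but it concerns a secondary outcome; the primary blood pressure analysis has a measured baseline and is not affected.

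**What to change.** In section 3.13, exempt the composite from the T1/T3/T5 change model and state its own analysis: first event (death from any cause, or admission for one of the three named causes) between randomisation and month 12. Count each participant once, combine the month-6 and month-12 reports, and count deaths whether or not later visits were completed. Compare the arms with a mixed model for a binary outcome with pharmacy as a random effect. Pre-enrolment admission may enter as a baseline covariate, but not as the T1 value of the outcome. Keep the change model for outcomes measured at baseline.

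In section 3.10, remove the completer restriction for this outcome so that it agrees with intention to treat.

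The month-6 and month-12 assessments of the composite are already in Table 2, so no patients or visits are added. The six-month hospitalisation item in section 3.7 is listed only for baseline and month 12, so the text should confirm that admissions in the first six months are captured at the month-6 assessment. The cost is a few sentences.
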